Participants who allocate to the intervention group will receive this program of interventions, which will be based around setting a quit date within 30 days of randomization. As described above, they will receive regular, personalized text messages providing smoking cessation advice, support and distraction. This content will also cover information relevant to quitting—for example, symptoms to expect on quitting, tips to cope with craving, tips to avoid weight gain and improve nutrition; advice on avoiding smoking triggers; instructions on breathing exercises to perform instead of smoking; motivational support (for example feedback on amount of money and life years saved) and distraction (for example, general interest, sports, fashion, trivia, travel). The messages will be developed by a multidisciplinary team including young adults, health related researchers and experts in cognitive behavioral therapy, and smoking cessation. An algorithm based on keyword matching will be developed to match participant characteristics (preferences, smoking history, barriers to cessation, etc.) with a database of over 1000 text messages so that an individualized program will be provided.

A quit day will be negotiated with each participant, and five messages will be sent per day for the time leading up to the quit day and the following 12 weeks. On the quit day, a free month of outgoing text messaging also begins, with participants encouraged to tell all their friends and family they are quitting on that day. This process will encourage communication and support, and also help with distraction, given the time that will spend in writing and receiving text messages. Several other text message based services will also be provided for the intervention group: Quit buddy (participants with similar characteristics and quit days will be put in touch with each other); text crave (participants could ‘pull’ text messages on demand by sending a text message to a short code number and they would receive a tip on how to get through their cravings); and TXT quizzes (questions will be sent out, following by answers the next day).

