Twelve weeks after randomization, coinciding approximately with the end of the free text messaging month, the intervention will become much less intensive, with the number of sent text messages reduced from five per day to three per week until the end of the 24 week (that is, six month) follow up. These messages will focus on maintaining cessation among those who had quit. Control group participants only will receive one text message every week, thanking them for being in the study, providing study centre contact details, and reminding them of the time until their free month at the end of follow up.

Anyone who completes follow up (a total of 24 weeks) will be rewarded with a free month of text messaging and 100 CNY mobile phone based payment (whether they quit or not), a reminder of these benefits will be sent to the participants at the beginning of the study and each month. All participants will be checked at 4, 8, 12, 16, 20, 24 week points about continuous smoking abstinence, point prevalence of abstinence, how many cigarettes per day during the last 4 weeks and past 1 week if they are still smoking, levels of craving, weight and so on. Symptoms of anxiety and depression, sleeping quality will be only asked at before quit day, 8 week, and 24 week points, and a phone call will be made for their significant other (e.g., family member, friend) to make a further confirmation about their quit status.

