### Statistical methods

**Power estimation:** On the basis of the results of the recent review paper [20] and the large sample size study published in the Journal of Lancet [15], we estimated that the control group quit rate would be around 5 % (ranged from 4.9 to 27.6 %) and loss to follow-up will be 10 %, with 95 % as an accepted standard for statistical significance. According to a power analysis, only 486 participants will be required in this group. However, given that none of the study from China, we plan to assess 4000 participants, and 2000 participants (1000 participants in each group) will be eligible and randomize to intervention or control groups. With 10 % loss to follow-up, we will have a 90 % of participants available for analyses, which will provide sufficient power to detect a difference.

**Comparison between Intervention group and control group:** For the data, *t* test, Chi-square test and logistic regression will be used for the comparison of the self-reported continuous smoking abstinence, point prevalence of abstinence, cigarettes smoked per day between the two groups. Repeated measures analyses of variance will be used for the comparison of levels of craving, weight, sleep quality, levels of anxiety and depression between the two groups. An alpha level of 0.05 (two-tailed) will be chosen for all statistical tests in this study. For the primary analysis we will use multiple imputation, which uses the observed predictors of outcome and the predictors of loss to follow-up to impute missing outcome data, thus attempting to correct for any potential bias caused by it (using the intent-to-treat principle, missing will be counted as smoker).

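### Repeated-measures ANOVA for craving, weight, sleep and mood keeps only people with every visit, and the first mood and sleep measurement is not fixed before randomisation

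*Protocol article*

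**What the plan says.** All references are to the protocol article.

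- **Method.** Statistical methods: "Repeated measures analyses of variance will be used for the comparison of levels of craving, weight, sleep quality, levels of anxiety and depression". No rule for missing values is attached to this sentence.
- **Missing data.** The same paragraph says: "For the primary analysis we will use multiple imputation". The intention-to-treat remark that follows counts missing people as smokers, so it concerns abstinence.
- **Expected loss.** The power paragraph assumes that "loss to follow-up will be 10" per cent, and concludes that "we will have a 90 % of participants available for analyses".
- **Visits.** Under Procedures, craving and weight are checked at weeks 4, 8, 12, 16, 20 and 24. Anxiety and depression follow the same timing as sleep: "sleeping quality will be only asked at before quit day, 8 week, and 24 week points".
- **Quit day and exposure.** Under Procedures, the quit date is set within 30 days of randomisation. In the intervention arm "five messages will be sent per day for the time leading up to the quit day" and for 12 weeks after it. Controls get one message a week.
- **Baseline.** Procedures has baseline data collected at the eligibility call, without listing the contents. Independent variables lists weight, sleep quality, anxiety and depression among characteristics collected by phone and questionnaire, without a time point.

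**The concern.** There are two separate weaknesses.

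The first concerns the method. Classical repeated-measures ANOVA needs a complete row per person, so one missed visit removes that person altogether. The only remedy in the text, multiple imputation, is reserved for the primary analysis. Followed as written, the plan would analyse these five outcomes in complete cases. With six follow-up calls for craving and weight, these could be far fewer than the 90% that the protocol counts on. They could also be a selected group, in a way that differs by arm.

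The second concerns timing. The only time given for the first mood and sleep score is before the quit day, and the quit day comes after randomisation. The wording therefore admits a first score taken after weeks of daily messages in one arm. If that score serves as the reference for change, part of any programme effect is already in it. A pre-randomisation score that was never taken cannot be recovered at the analysis stage.

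**Working it through.** **Inputs.** From Statistical methods: 2000 randomised, 1000 per arm, 10% loss. From Procedures: six follow-ups for craving and weight; two follow-ups plus one pre-quit measurement for mood and sleep; quit day up to 30 days after randomisation; five messages a day against one a week.

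**Step 1: the plan's own figure.** 2000 × (1 − 0.10) = 1800, or 90%. It reproduces. It equals the ANOVA sample only if all missing values belong to the same 10% of people.

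**Step 2: complete-case share.** Let *d* be the proportion missing at a visit and *k* the number of follow-ups. If the same people are missing throughout, the share is 1 − *d*. If misses are independent, it is (1 − *d*)^*k*. The first mood and sleep score is taken as complete.

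| *d* | Same people | Independent, *k* = 2 (mood, sleep) | Independent, *k* = 6 (craving, weight) |
|---|---|---|---|
| 5% | 95% | 0.95² = 90% (1805) | 0.95⁶ = 73.5% (1470) |
| 10% (planned) | 90% (1800) | 0.90² = 81% (1620) | 0.90⁶ = 53% (1063) |
| 25% | 75% | 0.75² = 56% (1125) | 0.75⁶ = 18% (356) |

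The 25% row is a sensitivity case. It comes from the pilot's follow-up target of at least 75% (Measures/Instruments) and is not a planning assumption of the main trial.

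**Step 3: precision.** Relative to 1800 analysed, the standard error grows by √(1800/1063) = 1.30 for craving and weight, and by √(1800/1620) = 1.05 for mood and sleep, at the unfavourable end of the 10% row. Under the same independent misses, nearly everyone has at least one follow-up value: 1 − 0.10² = 99% with two visits, and practically 100% with six. A model that uses all observed visits would keep them.

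**Step 4: direction of complete-case bias.** This was simulated with assumed values: three time points, 1000 per arm, within-person correlation 0.5, true effect −0.20 SD at both follow-ups, 400 replicates, and about 10% missing at week 24. The group-by-time contrast in complete cases was:

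- loss completely at random: −0.202
- loss dependent on a worse week-8 score in both arms: −0.193
- the same in the control arm only: −0.169
- the same in the intervention arm only: −0.225

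The bias runs either way.

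**Step 5: a late first score.** Up to 30 × 5 = 150 messages can precede the quit day in the intervention arm, against about 30/7 ≈ 4 in the control arm. Let *f* be the fraction of the effect already present at the first measurement. The group-by-time contrast is then (1 − *f*) × effect, and the group main effect over three time points is effect × (*f* + 2)/3.

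| *f* | Group-by-time: formula (simulated) | Main effect: formula (simulated) |
|---|---|---|
| 0 | −0.200 (−0.199) | −0.133 (−0.136) |
| 0.25 | −0.150 (−0.151) | −0.150 (−0.149) |
| 0.5 | −0.100 (−0.100) | −0.167 (−0.166) |
| −0.25 (early effect of opposite sign) | −0.250 (−0.249) | −0.117 (−0.116) |

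A late first score shrinks the group-by-time contrast if the early effect has the same sign as the later one, and exaggerates it if the sign is opposite. The main effect moves the other way. The protocol does not say which term is tested.

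**The case against.** The protocol nowhere says that people with a missed visit are dropped. That is a property of the classical procedure, and missing-data handling for additional scales is commonly left to the analysis plan. This stands as a caution about wording, but it does not remove the point. The method itself is fixed here, and the remedy beside it is expressly limited to the primary analysis.

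A reader might infer four stronger things, which the text does not support.

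- **That the ANOVA contradicts intention to treat.** That phrase belongs to the primary abstinence analysis and is spelled out as counting missing people as smokers. It has no meaning for craving, weight, sleep or mood.
- **That the first mood and sleep score is definitely post-randomisation.** A score taken at the eligibility call is also before the quit day, and the Procedures and Independent variables sections are compatible with it. The time point is unfixed, not shown to be contaminated.
- **That the bias is towards no effect.** The direction depends on the term tested, the sign of any early effect and the missingness mechanism.
- **That averaging in a pre-quit score dilutes all five outcomes.** No pre-quit craving score is scheduled, so the dilution argument does not apply to craving. The open question about the first measurement concerns mood and sleep.

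It is also fair to say that independent misses are an unfavourable assumption. Missed calls tend to cluster within people, so the share should lie between the two ends given.

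**Conclusion.** The point holds as a weakness in how additional outcomes are analysed and timed. Followed as written, repeated-measures ANOVA would analyse 53% to 90% of participants for craving and weight and 81% to 90% for mood and sleep at the planned 10% loss. The lower ends assume independent misses and a complete first score. The consequences are lost precision and a possible bias of unknown direction; the simulated sizes rest on assumed correlation, effect and dropout. Separately, the wording permits, but does not establish, a first mood and sleep score up to 30 days after randomisation and during messaging. If it were used as the reference, a group-by-time comparison would be distorted.

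These scales are not among the outcomes defined under Outcome measures (continuous abstinence, point prevalence and cigarettes per day). The primary abstinence conclusion is unaffected. The change is worth making because it is nearly free and because the timing part can only be settled before data collection.

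**What to change.** 1. Replace the repeated-measures ANOVA with a linear mixed model for repeated measures on all observed follow-up visits. Use arm, visit, arm-by-visit interaction, the baseline value where collected, and the minimisation factors (sex, age, education, Fagerstrom score) as fixed effects. Report the week-24 contrast between arms. This keeps everyone with at least one follow-up value. It is valid when missingness depends on observed values, as in the simulated dropout above, but it does not cure loss that depends on unobserved scores.
2. State that the first sleep, anxiety and depression scores are taken at the existing baseline call, before randomisation. Do the same for craving and weight if they are to serve as baseline covariates.

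The cost is a change of wording and a somewhat longer baseline call. No visit is added and the sample size does not change.

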### Pilot study

The following research activities with 10 % of the whole sample size (about 200 participants) will be conducted during pilot study. Flowchart for the pilot study shows in Fig. 3 and main study in Fig. 4.

**Fig. 3 Fig3:**
[figure not shown]
Development of ‘Happy Quit’ text messaging program flow. Control group: participants from control group will only receive one text message every week, thanking them for being in the study, providing study centre contact details, and reminding them of the time until their free month at the end of follow up

**Fig. 4 Fig4:**
[figure not shown]
Flowchart of program profile

**Develop the ‘Happy Quit’ program:** Development of smoking cessation text messages (detailed can be seen in Tables 1 and 2.) will be based on previous studies in other countries, and smokers and smoking cessation professionals in China. Questions for assessing program acceptability show in Appendixes (page35). It will take two to three months to develop the program.

**Assess the efficacy of ‘Happy Quit’ intervention:** The pilot study will be implemented with approximate 200 participants (100 participants in intervention group and 100 participants in control group), and feedbacks (such as acceptability of smoking cessation text messages and number of messages/day) from experts, providers and participants will be collected to improve the quality of ‘Happy Quit’ program. In this single-blind, 24-week, randomized trial, Participants will be allocated to either a control group or to a group that receives a supportive smoking cessation program.

**Examine the feasibility and acceptability of ‘Happy Quit’:** The feasibility and acceptability of the ‘Happy Quit’ program will be examined during the whole period of the pilot study stage. Examinations will include test-retest reliability and internal consistency of the instruments, acceptability of the message contexts, significant differences of intervention efficacy among smokers with different age and educational level, and decreased number of smoked cigarettes after intervention.

### Study status

Library of short messages for ‘Happy Quit’ program has be built, which began to develop in January 2016. Recruitment and data collection for this study will begin in April 2016 and will continue for the next two years.

## Discussion

Tobacco use is a major cause of disease burden and the number one preventable cause of death in the world. About one-third of the world’s tobacco is produced and consumed in China. Among the general population of smokers, most report a desire to quit. Unfortunately, the availability of smoking cessation programs in China is extremely limited, and the majority of cessation attempts end in relapse. The rapid development of mobile health technology (mHealth) provides unprecedented opportunities for improving health services and reaching underserved populations, and the effectiveness of text message mobile phone program on improving smoking cessation has been reported in other countries.

With relative large sample size, an mHealth Smoking Cessation Trial for individuals who subscribed to Nokia Life Tools showed that text message–based smoking cessation intervention can be successfully delivered in China and is acceptable to Chinese smokers [21]. However, this study had high opt-out rates and low postintervention response rates. Another study, relatively small sized sample (92 participants in the intervention group and 87 participants in the control group), evaluated the effectiveness of a mobile phone text-messaging based smoking cessation intervention package among Chinese adolescent smokers aged 16–19 years from six schools, which showed that the interactive and tailored assistance provided by the mobile phone text-messaging was effective in smoking intervention in Chinese adolescent smokers [22]. In this proposal, interactive and tailored will be provided for adult smokers. To the best of our knowledge, this is the first large sample size trial using interactive and individualized mobile phone-based text message interventions for adult smoking cessation in China. This proposed study could have widespread implications for tobacco control and health promotion in China, and can provide valuable experiences involving smoking cessation in China. We will submit a report to the Chinese Center for Disease Control and Prevention (China CDC), and distribute detailed reports on program development, intervention instruments and results of our evaluation to other administrations and organizations who are interested in promoting tobacco control in China.

However, there are some limitations in this proposal: First of all, this proposal will not provide biochemical verification for self-reported claims of abstinence due to the geographic spread of the sample, cost and other practical concerns. However, false reporting is considered to be minimal when there is little or no personal contact between treatment provider and participants (i.e. only through telephone); hence, it not likely that misreporting could compromise conclusions. Furthermore, the biochemical tests are not perfect. Cotinine has an in-vivo half-life of about 20 h, and can only be detected with a cotinine test for a few days after the use of tobacco. Carbon monoxide can be detected only for about 24 h after tobacco use. Secondly, although efforts will be made to ensure that the research staff remain be masked to whether a participant will be in the intervention or control group, occasionally trial participants would reveal this information to the study staff. This information could bias our estimates of self-reported abstinence. Thirdly, participants who will be allocated to the control group could reduce their motivation to quit. In order to address this issue, the control group will be recommended to receive smoking cessation care once the study is over. Despite those limitations, the expected benefits of this research project are numerous, such as providing interactive and individualized mobile phone-based text message smoking cessation program, developing suitable mhealth model in China, promoting mhealth in smoking cessation and other mental disorders’ treatment and prevention.

## Abbreviations

mHealth: The use of mobile information and communication technologies for improving health
SMS: Mobile phone based short text messaging service
